## Abstract

Children with speech sound disorders benefit from feedback about the accuracy of sounds they make. Home practice can reinforce feedback received from speech pathologists. Games in mobile device applications could encourage home practice, but those currently available are of limited value because they are unlikely to elaborate “Correct”/”Incorrect” feedback with information that can assist in improving the accuracy of the sound. This protocol proposes a “Wizard of Oz” experiment that aims to provide evidence for the provision of effective multimedia feedback for speech sound development. Children with two common speech sound disorders will play a game on a mobile device and make speech sounds when prompted by the game. A human “Wizard” will provide feedback on the accuracy of the sound but the children will perceive the feedback as coming from the game. Groups of 30 young children will be randomly allocated to one of five conditions: four types of feedback and a control which does not play the game. The results of this experiment will inform not only speech sound therapy, but also other types of language learning, both in general, and in multimedia applications. This experiment is a cost-effective precursor to the development of a mobile application that employs pedagogically and clinically sound processes for speech development in young children.

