### Outcome measurement

The relative benefits of the different experimental conditions will be measured by the primary measure of changes in use of phonological processes and PCC from pre-test to post-test as measured by the DEAP (Dodd et al., 2002). Such assessment will capture suppression of the phonological processes targeted in treatment and generalization effects (if any) to other phonological processes. Phonological process percentage of occurance (Randolph and Wendt, 2014; i.e., the number of times that a child uses a given phonological process) will also be measured and compared pre and posttest. Pre and post-test assessments will be recorded and a sample of the assessments independently analyzed followed by interrater reliability checks. In addition to the pre-test/post-test measures, number of trials and percentage accuracy of trials per session (cumulative accuracy) will be measured for each experimental condition as further indication of the effectiveness of feedback of that condition and determine when goals of intervention have been reached. For example, if a child reaches 90% accuracy of production of target words for one phonological process, another will be targeted. It could be argued that motivation to continue playing will increase practice and consequently improve outcomes (Williams, 2012). A secondary measure of motivation as a variable that could influence the effectiveness of feedback type will be the amount of time participants choose to continue playing the game (Deci et al., 1999) up to a total of 20 min as well as the number of trials they complete.

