## Proposed analysis

The assessments of speech production will be transcribed to an Excel spreadsheet. Statistical analysis will be performed using the Statistical Package for the Social Sciences (IBM SPSS Statistics 24).

The key question to be addressed in this research is: How does feedback type during speech therapy session influence children's production performance. As such, the key dependent variable under analysis will be PCC, phonological process percentage of occurrence and percentage accuracy of trials. Published data of PCC in children's development (e.g., Dodd et al., 2002) suggest that this variable to be normally distributed. As such we intend to perform a full-factorial regression analysis on PCC with feedback condition, number of trials completed, and child age (4, 5, or 6 years) and severity as predictor variables. The full-factorial nature of this analysis will allow us to determine how the effects of condition and trials completed independently predict PCC and the extent to which these factors interact in their effects on PCC between pretest and post-test. For example, we may find that with certain types of feedback, the number of trials completed has a much greater effect than with other types of feedback. Similarly, we may find that some feedback types have a greater effect on performance for younger or older children. These analyses will also be completed with phonological process percentage of occurance at pretest and post-test and percentage accuracy of trials as a dependant variables

We will also conduct a Generalized Linear Model Analysis assuming a binomial distribution for the number of correct trials post “intervention” within a total of *n* trials where *n* may differ between children. The analysis will control for pre “intervention” language skills, age, and gender. Marginal means will be compared for the five groups using a Bonferroni correction for multiple comparisons. This analysis could assist in distinguishing the effects of real-world simulation vs. verification feedback and the presence of articulation guidance.

Motivation to persevere could be considered a variable that mediates the impact of type of feedback. Consequently, we will also perform a one-way ANOVA to determine how feedback condition influences motivation as measured by the number of trials and the duration of game play.

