## Anticipated results

With respect to research question 1, this study aims to investigate the effectiveness of four different types of feedback in improving speech sounds in young children while using a multimedia platform. Each of the three theoretical frameworks for learning discussed in the Background section predict that KR, the prevalent feedback in speech learning applications, will be the least effective because it does not contain information to assist learners in improving their speech production (Shute, 2008). The conversational framework for multimedia learning predicts that intrinsic feedback will be more effective than KR feedback because it is most likely to resemble real-world speech learning experiences which can be built upon (Laurillard, 2002). This framework predicts that the most effective feedback overall will be intrinsic combined with topic contingent KP because children will be able to elaborate and refine knowledge gleaned from real-world experiences with lessons learned during speech pathologist/learner dialogue (Laurillard, 2002). Within the context of novice-expert learning (Mason and Bruning, 2001; Moreno, 2004) children who are more responsive to therapy (influenced by factors such as age and severity of disorder) might benefit from KR combined with topic contingent KP, possibly because they could benefit from smaller amounts of more focused feedback. This combination is also prevalent in speech pathology practice.

With respect to research question 2, the prediction that the two conditions with intrinsic feedback will be the most effective in improving speech production is accompanied by the prediction that these two conditions will also be the most motivating because they will be situated in natural and social scenarios that could be more visually appealing, possibly more challenging (Mayer, 2014b) while offering greater autonomy and relevance (Ryan et al., 2006) and consequently should encourage more trials and longer gameplay. We also anticipate that other features of the respective feedback types will emerge from the analysis to suggest variables that will improve their effectiveness.

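### The only analysis of PCC by feedback condition includes number of trials completed, a post-randomisation variable that condition is expected to change and that controls do not have

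*Protocol article*

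**What the plan says.** The key question in the Proposed analysis section is "How does feedback type during speech therapy session influence children's production performance". Research question 1 likewise asks how effective the feedback types are. For PCC the plan is a "full-factorial regression analysis on PCC with feedback condition, number of trials completed", plus age and severity. The model is meant to "determine how the effects of condition and trials completed independently predict PCC" and to show how the two interact. The same analysis is to be run for phonological process percentage of occurrence and for percentage accuracy of trials.

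Elsewhere the protocol treats trial count as a result of condition:

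- Session schedule: the number of trials is not fixed, and children decide when to stop the experimental activity.
- Proposed analysis: "Motivation to persevere could be considered a variable that mediates the impact of type of feedback". A one-way ANOVA is to examine "how feedback condition influences motivation as measured by the number of trials and the duration of game play".
- Anticipated results: the two intrinsic conditions are predicted to be more motivating and "consequently should encourage more trials and longer gameplay".
- Abstract: the arms are "four types of feedback and a control which does not play the game". Table 4 gives not applicable for the control arm throughout.

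**The concern.** Randomisation supports a comparison of the arms as allocated. Number of trials arises after allocation and may itself be changed by allocation, so holding it fixed has two consequences.

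First, if a feedback type helps partly because children practise more, that part of its benefit is credited to trials and not to condition. Second, children who complete many trials probably differ in attention, persistence or ability from those who complete few. If intrinsic feedback raises trial counts, comparing arms at equal counts means comparing different kinds of children.

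The control arm adds a third difficulty. The Design section includes it to account for change over time from natural development or other interventions, but it has no trial counts to enter in the model. At stake is whether any planned analysis gives the randomised effect of feedback on PCC, which is what research question 1 asks for.

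**Working it through.** **1. Which planned analyses could give the effect of condition on speech outcome?**

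| Analysis (Proposed analysis section) | Outcome | Trials in the model? |
|---|---|---|
| Full-factorial regression | PCC; repeated for process occurrence and percentage accuracy | Yes, crossed with condition |
| Binomial generalized linear model | Number of correct trials | Not as a covariate |
| One-way ANOVA | Number of trials; duration of play | Trials are an outcome |

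No row estimates the effect of condition on PCC, or on process occurrence, without trials.

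**2. Can the control arm be fitted?** Suppose control trials are coded zero.

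- Condition by trials: 5 intercepts + 5 slopes = 10 columns. The control slope column is all zeros, so the rank is 9 and that slope cannot be estimated.
- Full factorial with age (3 levels) and severity (3 levels): 5 × 3 × 3 = 45 cells, and with a slope in each, 90 columns for 150 children. The 3 × 3 = 9 control slopes cannot be estimated, so the rank is at most 90 − 9 = 81. One simulated allocation gave 73, because some cells were empty or too small.
- The additive model (condition + trials) has 6 columns and full rank. It compares game arms with control only by projecting the game arms to zero trials. The Session schedule expects 80–100 trials per session, which over 12 sessions is 960 to 1,200 in total, so the projection is far from the data.

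If control trials are coded missing, a complete-case regression drops the control arm.

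**3. How far could the intrinsic-versus-KR contrast move?** The protocol gives none of the quantities needed, so these are assumptions: mean total trials 1,000 under KR and 1,100 under intrinsic (both inside 960–1,200), within-arm SD 200, 2 PCC points per 100 trials, and a direct effect of intrinsic feedback of 2 points.

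- Total effect = direct + slope × gap = 2 + 0.02 × 100 = 4 points.
- Contrast at equal trials, no confounding = 4 − 0.02 × 100 = 2 points. Simulation of five arms of 30, with trials as an additive covariate, agreed: 4.02 without trials in the model and 2.04 with them.

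Now add an unmeasured trait that correlates r with trials and shifts PCC by λ points per SD. The fitted trial slope rises by λ × r / SD, so the adjusted contrast falls by a further

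λ × r × gap / SD = λ × 0.5 × 100 / 200 = 0.25 λ.

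| λ (PCC points per SD of trait) | Further bias | Reported contrast (true total 4) |
|---|---|---|
| 0 | 0 | 2.0 |
| 4 | −1.0 | 1.0 |
| 6 | −1.5 | 0.5 |

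The further bias is the same when neither feedback nor trials has any true effect on PCC. The adjusted contrast would then be −1.0 to −1.5 where the truth is 0. Both components scale with the trial gap: at a gap of 50 they are halved (mediated part 1 point, further bias 0.125 λ), and at a gap of 0 they vanish.

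**4. Limiting case.** If feedback works only through practice (0.1 point per trial; mean trials 80 under KR, 100 under intrinsic, 0 in control), the true effects are 0.1 × 20 = 2.0 for intrinsic minus KR and 0.1 × 80 = 8.0 for KR minus control. With trials in the model, simulation returned −0.04 and −0.14, so both effects disappear.

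**The case against.** The strongest defence is that the trials term is deliberate. Research question 2 asks which variables influence the effectiveness of each feedback type, and the Outcome measurement section speaks of "A secondary measure of motivation as a variable that could influence the effectiveness of feedback type", which is the language of a moderator. A condition-by-trials interaction is a reasonable way to explore that. This stands, and it is a reason to keep the analysis. It does not make that model an answer to research question 1.

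Second, the binomial model compares marginal means for all five groups without trials as a covariate. A reader might infer that no group comparison free of trials is planned at all; that would be wrong. But its outcome is the number of correct trials, not PCC or process occurrence.

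Third, a reader might infer that the model removes the main mechanism the investigators predict. The Anticipated results section does not support this. For question 1 the predicted mechanism is informational: KR carries no information to guide the child, and intrinsic feedback resembles real-world experience. More practice is an accompanying prediction under question 2. Adjusting for trials takes out the practice route, not the informational one.

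Fourth, the documents do not state that controls have zero trials; Table 4 says not applicable. Nor do they rank the analyses, so this regression is the first listed and the only one for PCC, not a declared primary analysis.

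Fifth, the Session schedule says trial counts will be checked for equity between participants. Checking does not fix the number, and the protocol itself predicts a difference. Last, a separate analysis plan might add a trials-free model. The difficulty here is a stated model that does not match the stated question, not detail left out.

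**Conclusion.** The point holds. As written, no analysis gives the randomised effect of feedback condition on PCC or process occurrence. The condition terms describe differences at a given trial count, which excludes any practice route and is open to confounding. Contrasts with control are either extrapolated or lost, depending on how not-applicable trial counts are coded.

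The structural results (rank 9 of 10; at most 81 of 90) follow from the design once control trials are coded zero. The PCC figures are illustrations: a true 4 points reported as 2, with a further 1.0 to 1.5 points of bias for trait effects of 4 to 6 points per SD. They rest on an assumed trial gap, SD, slope and correlation, and on an additive model without age and severity. Those two planned predictors would absorb some of the confounding. No standard errors or false-positive rates are given, because they depend on a residual SD for PCC that the protocol does not report. The figures should not be read as forecasts for this trial.

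**What to change.** **For research question 1:** estimate the effect of condition on post-test PCC, and on post-test process occurrence, in all five arms without number of trials. Adjust for the pre-test value, age and severity as main effects. If the condition × age × severity factorial is kept, report marginal condition means averaged over age and severity. Deleting trials alone would still leave 45 cells for 150 children and, under default coding, condition coefficients that refer to a single age-and-severity cell.

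**For research question 2:** keep number of trials, play time and the condition-by-trials interaction in a separate secondary mediation or dose analysis, restricted to the four game arms and labelled as non-randomised evidence.

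**Cost:** a change of analysis wording and slightly more analysis work. No new data and no change to the design or sample size.

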## Materials and equipment

### Participants

Children aged between 4 and 6 with phonological delay or phonological disorder as identified by a qualified speech pathologist using the Developmental Evaluation of Articulation and Phonology (DEAP; Dodd et al., 2002) will be randomly allocated to five groups, each with 30 participants. Phonological delay is defined as the consistent use of phonological processes that are used in typical development that are supressed by 90% of children of the same chronological age (Dodd, 2014). Phonological disorder was defined as the consistent use of phonological processes in which some of the phonological processes used by that child are not used by 90% of children at any stage of their development (Dodd, 2014). The children will all consistently use one or more of the three phonological processes to be targeted by the intervention of this study (stopping, fronting or cluster reduction). The severity of each child's diagnosis will be either mild, moderate or severe with reference to the normative data for percentage consonants correct (PCC) as measured by the DEAP.

All children will be monolingual English speakers with receptive language within or above the expected range for their age as measured by the Clinical Evaluation of Language Fundamentals –Preschool 2nd Edition (Wiig et al., 2006) or Clinical Evaluation of Language Fundamentals –Fourth Edition (Semel et al., 2006). Children will have hearing skills within normal limits as measured by their last hearing test within the last 12 months and will not have other symptoms of developmental delay as reported by parents. The children will also have no apparent deficits in structure and function in oromotor structure and function as determined by examination by a speech pathologist.

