### Recruitment of participants

Potential participants will be identified from the Australian Catholic University Speech Pathology in Schools program in Melbourne. This program operates in several Catholic Education Primary Schools in Melbourne. Parents of clients of this service who are identified as having a phonological delay or disorder will be provided with an information sheet about the study. Parents who wish for their children to participate will be required to contact the staff of the study. Additional participants will be recruited through advertisement in kindergartens, day-care centers and playgroups.

Stratified random sampling based on severity of speech disorder and will be used to allocate children to experimental conditions. This process will ensure that each condition includes similar proportions of children with either a mild, moderate or severe phonological disorder. Due to the nature of the intervention, participants and therapists cannot be blinded to the experimental condition. However, pre- and post-test assessments of speech production will be carried out by a researcher/therapist blind to the assigned condition.

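### Neither planned model lists continuous pre-test PCC as a covariate, and the binomial model also omits the severity stratum; the loss is small if change is analysed, large if post-test PCC alone is

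*Protocol article*

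**What the plan says.** Proposed analysis plans a factorial regression of PCC in which feedback condition and the trial count are joined by "child age (4, 5, or 6 years) and severity as predictor variables". It says that this will show "the extent to which these factors interact in their effects on PCC between pretest and post-test". It does not say whether the dependent variable is the post-test score, the change score or a repeated measure. The same analysis is to be run on process occurrence at both test points.

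Outcome measurement describes the "primary measure of changes in use of phonological processes and PCC from pre-test to post-test".

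Under Participants, each child's severity is "mild, moderate or severe with reference to the normative data for percentage consonants correct (PCC"), as measured by the DEAP. Recruitment of participants allocates children by "Stratified random sampling based on severity of speech disorder".

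A second analysis in Proposed analysis is a binomial generalized linear model for the number of correct trials after the intervention. It controls for pre-intervention "language skills, age, and gender" and compares the five group means with a Bonferroni correction.

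**The concern.** Every child takes a DEAP pre-test, so a continuous baseline exists for the main outcome. The PCC regression carries that baseline on the predictor side only as mild, moderate or severe. Differences between children within a band then stay in the error term, as does any chance imbalance within bands between arms.

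The binomial model is more exposed. Its outcome is a post-intervention count with no pre-test value subtracted, and its covariate list leaves out the factor used to stratify allocation. The language-skills covariate is not defined. The only language test that the article describes is a receptive-language test, which is a different construct from speech accuracy, and inclusion restricts its range to scores within or above the expected level.

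At stake is precision in comparing five arms of 30 children.

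**Working it through.** **The plan's own figure.** The article gives N = 150 for f = 0.32, 5% significance and 80% power. A one-way test of five groups (noncentral F, λ = N·f²) needs 122 children, or 125 in equal groups, and has 88.8% power at 150. An omnibus regression test with 7 predictors and f² = 0.1024 needs 148. The article does not name its test. The stated size errs on the safe side for the one-way test, and the point here does not depend on it.

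**Inputs.** From the article: three PCC-based severity bands, 150 children, and the two covariate lists. Assumed, because the article gives neither: the pre-post correlation ρ of PCC and the share of children in each band. Pre-test and post-test PCC are taken as jointly normal with unit variance.

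**Baseline variance captured by the bands.** For equal thirds of a normal baseline, the bands explain R² = 0.793. For a 70/20/10 split, R² = 0.629.

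**Residual variances.**
- Continuous pre-test as covariate (outcome post-test or change): 1 − ρ²
- Post-test score with bands: 1 − ρ²R²
- Change score with bands: (1 − ρ)²(1 − R²) + 1 − ρ²

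Equal thirds:

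| ρ | Continuous pre-test | Post-test with bands | Ratio | Change with bands | Ratio |
|---|---|---|---|---|---|
| 0.7 | 0.51 | 1 − 0.49 × 0.793 = 0.611 | 1.20 | 0.09 × 0.207 + 0.51 = 0.529 | 1.04 |
| 0.8 | 0.36 | 1 − 0.64 × 0.793 = 0.492 | 1.37 | 0.04 × 0.207 + 0.36 = 0.368 | 1.02 |
| 0.9 | 0.19 | 1 − 0.81 × 0.793 = 0.358 | 1.88 | 0.01 × 0.207 + 0.19 = 0.192 | 1.01 |

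On the post-test reading, 150 children carry the information of about 150/1.20 = 125, 150/1.37 = 109 or 150/1.88 = 80. On the change reading the loss is 1% to 4%.

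**Sensitivity.**
- With a 70/20/10 split and ρ of 0.7, 0.8 and 0.9, the post-test ratios are 0.692/0.51 = 1.36, 0.597/0.36 = 1.66 and 0.491/0.19 = 2.58. The change-score excess falls from about 6.5% to about 2%.
- At lower correlations with equal thirds, the two readings coincide at ρ = 0.5 (0.802/0.75 = 1.07). At ρ = 0.3 the change score loses more (1.011/0.91 = 1.11) than the post-test score (0.929/0.91 = 1.02).
- In no case tried does continuous adjustment leave more residual variance than the bands.

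**Power at N = 150, post-test reading, equal thirds.** Here f is the effect before adjustment, divided by the square root of the residual variance.
- f = 0.32, ρ = 0.6: 97.0% with bands, 98.3% with the continuous pre-test.
- f = 0.25, ρ = 0.7: 88.7% with bands, 94.0% with the continuous pre-test.

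**Binomial model.** The article gives nothing from which to size the loss, so the comparison is of text only. Allocation is stratified by severity, and severity is not in the covariate list. No baseline speech measure is named there either.

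**The case against.** The strongest reply is that the baseline is already used. Outcome measurement defines the primary measure as change from pre-test to post-test, and Proposed analysis speaks of effects between the two tests. If change is the dependent variable, the pre-test enters through the outcome and the bands cost only a few percent. This stands. A reader might infer that the severity bands are the only place where baseline PCC enters the regression, or that the trial simply behaves as if it had 80 to 125 children. The article supports neither, since no sentence says that post-test PCC alone is modelled.

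It can also be said that stratified allocation already balances severity across arms, so only imbalance within bands remains, and that the age-by-severity terms of a full-factorial model may recover some further baseline information. Both are fair and could make the loss smaller than computed. On the less favourable outcome reading, power in the two cases above still stays over 80% with bands alone.

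For the binomial model, a reader might infer that baseline speech accuracy is certainly excluded. Because the language-skills covariate is undefined, the article shows only that such a measure is not named. The omission of severity does stand, since the list is explicit and severity is not on it. That this is an additional analysis does not remove the point: it is the one for which corrected comparisons of all five groups are specified.

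Finally, Session schedule places the pre-test after allocation, which might seem to disqualify it as a covariate. It precedes treatment, and Recruitment of participants has it done by an assessor blind to condition, so it remains valid.

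**Conclusion.** The point holds as one of efficiency and of unclear specification; no bias is shown in the main regression. Continuous pre-test PCC is in neither covariate list, and the stratification factor is missing from the binomial model. With equal thirds and ρ of 0.7 to 0.9, the excess residual variance in the PCC regression is about 1% to 4% on the change reading, which the article's outcome definition favours, and 20% to 88% on the post-test reading. These sizes rest on an assumed correlation, assumed band shares and normality. The direction was the same under every assumption tried. The loss in the binomial model cannot be sized from the article.

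**What to change.** State the form of the outcome. Analyse post-test PCC, and post-test process occurrence, each with its matching continuous pre-test value as a covariate, and keep the planned condition, age and severity terms. Enter the pre-test value as a main effect only, so that it does not enlarge the factorial. The role of trials completed and its interactions, which serve the second research question, is a separate matter that this change leaves untouched.

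In the binomial model, add pre-test PCC and the severity stratum, and say which measure the language-skills covariate is.

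The cost is analysis wording only. No visit, test or child is added. Stating the model this way also settles the choice between change and post-test score, and it is at least as precise as the banded analysis under either.

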### Research questions

How effective are different types of feedback in improving speech sounds in young children while using a multimedia platform?What variables influence the effectiveness of each type of feedback?

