### Stimuli

Targets for intervention will be minimal pairs addressing the phonological processes of stopping, velar fronting and cluster reduction as, according to Dodd et al. (2002) 90% of children over 3;11 (3 years and 11 months of age) will have suppressed these phonological processes and they are therefore considered errors at this stage.

The target words comprising the minimal pairs will be:
High frequency, high imageability wordsExclude the consonants /∫/ (“sh”), /θ/ (voiceless “th”) and /ð/ (voiced “th”) as, according to Dodd et al. (2002) 90% of children by the age of 4;0 can produce all consonants except these.Exclude words with triclusters (i.e., words with three sounds in a consonant cluster such as “splash”)Initial word position as people tend to identify initial sounds more readily than medial or final sounds (Redford and Diehl, 1999).

For each phonological process addressed, five different examples for each minimal pair will be included as stimuli in the experimental tasks. For example, an experimental task targeting stopping could include the minimal pairs “fin-pin,” “see-tea,” “zoo-do,” “fat-pat,” and “zip-dip.” Hodson (2010) suggested that at least two exemplars of each phonological process be targeted in therapy. In total, 15 minimal pairs will be addressed across the experimental activities. All minimal pairs will be matched for age of acquisition, imageability and concreteness based on the MRC Psycholinguistic database and frequency using the SUBTLEX-UK database (van Heuven et al., 2014).

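### Age enters the regressions in whole years, which costs some power for the question whether feedback works differently in younger and older children

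*Protocol article*

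**What the plan says.** The Research questions section asks, as its second question, "What variables influence the effectiveness of each type of feedback". The Proposed analysis section gives the model: "we intend to perform a full-factorial regression analysis on PCC with feedback condition, number of trials completed, and child age (4, 5, or 6 years", together with severity. The form of age in it is thus "child age (4, 5, or 6 years". The section gives age moderation as an example of what the model could show: "we may find that some feedback types have a greater effect on performance for younger or older children". The same regressions are then repeated for other outcomes: "These analyses will also be completed with phonological process percentage of occurance at pretest and post-test and percentage accuracy of trials".

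Eligibility, in the Participants section, is "Children aged between 4 and 6 with phonological delay or phonological disorder". The Stimuli section works at a finer age scale when it cites norms, for example "90% of children over 3;11 (3 years and 11 months of age) will have suppressed". The article nowhere plans to analyse age in months. The separate binomial model also controls for age, but no form is stated for it there.

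**The concern.** Whether a feedback type works better for younger or for older children is a question about an ordered, continuous quantity. Whole years treat a child of 4;0 and a child of 4;11 as the same age, and children of 4;11 and 5;0 as a full year apart. The age differences within each year are not used.

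A second cost depends on the coding. If age is a three-level factor, its interaction with five conditions uses (5 − 1) × (3 − 1) = 8 degrees of freedom. A single linear term needs (5 − 1) × 1 = 4.

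What is at stake is power for one moderator test under research question 2. The loss is separate from the size of the full-factorial model, because it remains in a model with only condition, age and their interaction.

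**Working it through.** **The plan's own figure.** The article gives no effect size or power for an age interaction, so there is no figure for this test to reproduce. Its one power statement is 150 children for f = 0.32, 5% significance and 80% power. For a five-group one-way ANOVA I get 122 children (125 with equal groups), and 150 children give power 0.89. The stated 150 is therefore not reproduced, but nothing below depends on it.

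**Inputs from the protocol article.** Five conditions of 30 children (N = 150); significance level 5%; age values 4, 5, 6.

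**Assumptions, not in the article.** Ages are evenly spread from 4;0 to 6;11. The condition-by-age effect is linear in exact age, and it is sized so that exact age gives 80% power.

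**Step 1: age variance kept by whole years.**
- Variance of an even spread over 3 years: 3²/12 = 0.750.
- Variance within one year: 1²/12 = 0.083.
- Share kept: (0.750 − 0.083)/0.750 = 0.889, that is 8/9. About 11% is lost.

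**Step 2: power of the condition-by-age test** (noncentral F, model with condition, age and their interaction).
- Age in months: 10 parameters, so F with 4 and 140 df. A noncentrality of 12.35 gives 80%.
- For a linear effect, whole years reduce the noncentrality to 12.35 × 8/9 = 10.98.

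| Coding of age | df | Noncentrality | Power |
|---|---|---|---|
| Months, linear | 4, 140 | 12.35 | 80% |
| 4, 5, 6 as a number | 4, 140 | 10.98 | 74.5% |
| 4, 5, 6 as three categories | 8, 135 | 10.98 | 61% |

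**Step 3: a different starting point.** If the interaction is instead given the article's f = 0.32, the noncentrality is 0.32² × 150 = 15.36. Power is then 0.89 with exact age, 0.84 with the numeric year score and 0.72 with three categories. The ordering is the same, with losses of about 4 and 17 percentage points.

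**Step 4: effect on the main comparison of conditions.** Assume 80% power for the 4-df condition test with exact age in the model, and let age explain 5% to 20% of the outcome variance (an assumed range). Whole years over 4;0 to 6;11 then leave power at about 79% to 80%.

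**The case against.** The strongest objection is that the coding is inferred. The parenthesis may only restate the enrolled age range. The word full-factorial does not settle the matter, since the number of trials, a count, is in the same list of predictors. A condensed article may also leave exact coding to a fuller plan. This stands in part: a reader might infer that age is certainly a three-level factor and take 61% as the result, but the text does not say so. It does list three whole-year values, and either way of using them loses information.

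Second, age moderation is offered as an example of what might be found, with no linear form stated. The comparison above assumes linearity, which favours months. This stands: three categories can follow a non-linear pattern, and the gap would then narrow.

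Three stronger readings are tempting, and the article does not support them.
- Enrolment might be thought to stop at the sixth birthday. Whole years would then keep only 75% of the age variance, and power with a numeric score would be about 66%. But the analysis section itself lists 6-year-olds, so this fits the text poorly.
- Coarse age might be thought to weaken the main comparison of conditions. Step 4 shows that the effect is negligible, and because allocation is randomised no systematic bias follows.
- The binomial model might be thought to share the fault. It names age as a covariate without a whole-year form, so no fault is shown there.

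**Conclusion.** The point holds as a limited loss of power in the regressions. As worded, they use age in whole years for a question about younger and older children. With 150 children, ages evenly spread over 4;0 to 6;11 and a roughly linear trend, power for the age-moderator test falls from 80% to about 74.5% (numeric score) or about 61% (three categories). The article does not say which coding is meant, and it gives neither an age distribution nor an effect size for the interaction. The size is therefore illustrative, while the direction is the same under both codings if the trend is roughly linear. Research question 1 is not threatened. The change is worth making mainly because it costs almost nothing.

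**What to change.** In the Proposed analysis section, replace "child age (4, 5, or 6 years" and its closing bracket with centred age in months at pre-test, entered as a continuous predictor. Name condition by age in months as the age-moderator test. Apply this to all the regressions in that section, including the repeats for the other outcomes. Check linearity with residual plots, and keep year bands for descriptive tables only. The binomial model can use the same form of age for consistency.

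The cost is one line of analysis wording. Date of birth and pre-test date are enough; no further children, visits or assessments are needed. The downside is the assumption of an approximately linear age effect over a narrow age range.
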